### Behavioural support for intervention groups

In both intervention groups, the SSS advisor is instructed to provide only behavioural support that is integral to the incentives intervention. In total, the interventions include the following four behaviour change techniques (BCTs), as defined by a standard taxonomy of BCTs [24], and the numbering is that used in the taxonomy:

10.1 *Material incentive (behavior):* Inform that a financial incentive will be offered if the participant and SOS reports not smoking and has a CO < 8 ppm

1.3 Goal setting (outcome): Set a goal of not smoking a single puff of a cigarette until the next assessment

2.6 Biofeedback: Inform the person of their expired CO reading

10.4 Social reward: SSS congratulates person if they remain abstinent from smoking

Adherence to the protocol for providing behavioural support will be been explored in the interviews with smoking cessation advisors.

### Payments for attending assessments

In addition, in order to maximise completion of follow-ups, all participants are offered a £20 voucher payment, for completing a follow-up assessment at both 3 months and 12 months postpartum (i.e. £20 for each assessment).

### Criteria for discontinuing or modifying allocated interventions {11b}

There are no special criteria for discontinuing or modifying allocated interventions.

Participants may choose to stop attending appointments and receiving incentive payments for any reason.

### Strategies to improve adherence to interventions {11c}

None beyond the brief behavioural support described in {11a}.

### Relevant concomitant care permitted or prohibited during the trial {11d}

Trial participants are permitted to receive relapse prevention support, during postpartum, beyond that provided by the intervention and any additional support is recorded. The SSS conducting the research follow-ups are asked not to provide any relapse prevention support at the follow-ups beyond that defined as part of the intervention (for the description of the allowed support see: {11} Intervention description/Behavioural support for intervention groups).

### Provisions for post-trial care {30}

None, beyond standard care within the NHS

### Outcomes {12}

At the 3 and 12 months postpartum follow-ups, women will initially be assessed for smoking status over the phone (up to five attempts will be made to call them) by their stop smoking service (SSS) advisor or by a researcher. Those who report having not smoked a single puff of a cigarette since their last quit date in pregnancy will be asked to attend a face-to-face appointment with their SSS advisor to confirm their smoking status or to confirm their smoking status by remote means (see section ‘Assessing smoking cessation outcomes during COVID-19 restrictions on face-to-face contact’).

### Primary outcome measure

The primary outcome is self-reported, lapse-free, smoking abstinence from the last quit attempt in pregnancy until 12 months postpartum, biochemically validated by an exhaled CO reading of < 8 ppm, and/or saliva cotinine or anabasine estimation. Where possible, both a CO reading and saliva sample will be collected and for a woman to be validated as abstinent both the CO reading and saliva test will need to confirm abstinence. Where both a CO reading and saliva sample cannot be collected, either a CO reading *or* a saliva test will be used to confirm abstinence. The proportion of abstinent women will be compared between the two intervention groups and between each intervention group and the control group. During pregnancy, due to physiological changes including higher metabolism [25], a CO cut-off of < 4 ppm is recommended [17, 18], whereas out of pregnancy a cut-off of < 8 ppm is more standard [19].

Where the expired CO reading is < 8 ppm, or a CO reading is not available, and the cotinine level is < 10 ng/ml [26], the participant is defined as a biochemically verified as abstinent. Where the CO reading is < 8 ppm, or a CO reading is not available, and the cotinine level is ≥ 10 ng/ml and the participant reports use of nicotine replacement therapy, e-cigarettes or heat-not-burn products, then saliva samples will be also tested for anabasine. Where the anabasine result is < 0.2 ng/ml [27], then the participant will be defined as a biochemically verified as abstinent.

Since recruitment to the study is conducted between 34 weeks gestation and 2 weeks postpartum, it is possible that a few women may relapse after recruitment and before giving birth. In the analysis for the primary outcome these women will not be distinguished from those who have relapsed after the birth. However, we will report the numbers of women who relapsed before the birth, separately for the two study groups.

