##### Payments to participants

Participants are offered a total of £60 of incentive payments. An incentive of £20 is offered at each of the visits at 1, 2 and 3 months postpartum. Payments are conditional on self-report of not smoking a single puff of a cigarette since their last quit date in pregnancy and an expired CO reading of < 8 ppm. This intervention, including the amount of incentive, was chosen because it has been used previously in the UK, including in Greater Manchester, and has been shown to be acceptable to postpartum women and SSS advisors [22].

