### Intervention group 2: incentives are offered up to 12 months postpartum

This intervention is provided in addition to the usual care as received by the ‘no incentives’ group.

In addition to all the incentives offered to group 1, participants in this group are offered £60 at each of the visits at 6, 9 and 12 months postpartum. The rationale for the amount of incentive offered in the 12-month condition was based on repeating the payment made to the participant at 3 months (i.e. £60) at 3-month intervals (i.e. at 6, 9 and 12 months) up to 12 months. Again, payments are dependent on expired CO confirmation of self-reported abstinence. No additional incentive is offered to the SOS beyond that offered at 3 months.

The total value of incentives offered to this group, including those offered to the participant (£240) and SOS (£60), is £300. This intervention was devised specifically for this study, in order to examine the potential benefit of continuing the offer of incentives, at 3-month intervals, up to the primary end-point at 12 months postpartum.

To our knowledge, neither of the incentive interventions has been previously tested in a research study. The level of incentives offered in the interventions are between the lowest level suggested by the general public that might be effective (£20 per month) and the highest acceptable level (£80 per month), for during pregnancy [23]. No such data on incentives is available for postpartum.

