### Assessing smoking cessation outcomes during COVID-19 restrictions on face-to-face contact

During COVID-19, for the 3- and 12-month postpartum outcomes for smoking cessation, if it is not possible to take an expired CO reading during a face-to-face visit, participants will take a CO reading using a self-administered/single-person use device (iCO^TM^ Smokerlyzer, Bedfont Scientific Ltd.) [28] and send the CO reading to the stop smoking advisor via an app. There is recent evidence that the iCO can produce a slightly higher CO reading than more conventional CO monitors [20]. However, the authors of this study recommend an optimal cut-off for the iCO of < 6 ppm; therefore, we decided to retain our more liberal cut-off of < 8 ppm.

If a participant joined the trial before the COVID-19 restrictions and therefore was not sent a self-administered CO monitor when they were recruited and a face-to-face CO reading is not possible, then a CO reading will not be collected at 3 or 12 months follow-up; at 3 months, abstinence will be self-reported alone and at 12 months self-reported abstinence will be validated, where possible, by a saliva test. The participant will be sent a salivette and instructions to provide a saliva sample and will be advised how to take a saliva sample during the follow-up call with the stop smoking advisor. The participant will then be asked to post the saliva sample to a laboratory for analysis (ABS Laboratories, Hertfordshire, UK, https://www.acmgloballab.com/about-us/our-locations/europe-london-uk). The follow-up questionnaires will be administered by the participant’s stop smoking advisor over the phone. When the COVID-19 restrictions have been lifted, we will give participants the option of continuing with the above approach or they can choose to have face-to-face appointments.

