### Assignment of interventions: blinding

#### Who will be blinded {17a}

Due to the nature of the intervention, participants and the SSS advisors delivering the intervention will not be blinded to the treatment received. Nor will SSS advisors or researchers who ascertain smoking status at 3 and 12 months postpartum be blinded; however, there is low risk of bias as smoking status is biochemically validated. Those involved in the data analyses will be blinded to the group allocation.

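### At 12 months only the 12-month arm is paid on a CO reading, and CO alone can confirm the primary outcome, so the unqualified low-bias claim is not supported

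*Protocol article*

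**What the plan says.** **Endpoint.** Under Primary outcome measure, the protocol article defines lapse-free abstinence "until 12 months postpartum, biochemically validated by an exhaled CO reading of < 8 ppm, and/or saliva cotinine or anabasine estimation". When both tests are collected, "for a woman to be validated as abstinent both the CO reading and saliva test will need to confirm abstinence". The fallback follows: "Where both a CO reading and saliva sample cannot be collected, either a CO reading" or a saliva test is enough. The second paragraph of the same section then lists the routes to being biochemically verified, and each of them includes a cotinine or anabasine result.

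**Payments at 12 months.** Under Intervention group 2, "participants in this group are offered £60 at each of the visits at 6, 9 and 12 months postpartum", and "payments are dependent on expired CO confirmation of self-reported abstinence". No saliva condition is attached. For the 3-month arm, "An incentive of £20 is offered at each of the visits at 1, 2 and 3 months postpartum", and nothing conditional on abstinence is offered to the participant after that. Control is offered none. All arms are offered £20 at 12 months for completing the assessment, whatever their smoking status.

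**Remote follow-up.** Under the section on outcomes during COVID-19 restrictions, the woman takes her own CO reading on the iCO and sends it by app, while saliva is posted to a laboratory. The section says the iCO can read slightly high and that "the authors of this study recommend an optimal cut-off for the iCO of < 6 ppm", yet keeps < 8 ppm.

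**Blinding.** Under Who will be blinded {17a}, advisors and researchers who ascertain smoking status are not blinded, but "there is low risk of bias as smoking status is biochemically validated".

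**The concern.** The low-bias statement rests wholly on validation. Validation is at its weakest when it is a single CO reading taken by the participant at home, and at 12 months that reading carries a £60 reward in one arm only. If the reward leads some relapsed women to report abstinence and pass on CO, and no saliva result is there to contradict them, they count as abstinent in that arm. The £20 paid to everyone does not offset this, because it rewards completing the assessment and not being abstinent.

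Any such error would favour the 12-month arm against both others. It matters most for 12 versus 3 months, which the Trial status section gives only 60% power at 154 per arm.

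**Working it through.** **1. Which women can be verified on CO alone?**

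| Situation at 12 months | CO-only verification possible? |
|---|---|
| Recorded as relapsed at 3 months | No, already counted as relapsed at 12 months |
| Seen face to face | Only if saliva cannot be obtained at the visit |
| Joined before the restrictions without an iCO, not seen face to face | No, CO is not collected; saliva is used where possible |
| Remote, with iCO, saliva returned | No, both must confirm |
| Remote, with iCO, no saliva result | Yes under the first paragraph of the outcome section; not by any route listed in the second |

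The exposed group is mainly the last row. The protocol gives no number for it. The article does not say outright that the £60 visit and the 12-month follow-up are one appointment, but both fall at 12 months and both use CO to confirm self-report.

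**2. The plan's own power figures.** Inputs: 9%, 22.6% and 36.2% abstinent, alpha 0.017 (Sample size), 154 per arm (Trial status). With a pooled-variance normal approximation and alpha taken as two-sided:

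- 300 per arm, 22.6% v 36.2%: 90.0% (stated 90%)
- 154 per arm, 22.6% v 36.2%: 59.3% (stated 60%)
- 154 per arm, 9% v 22.6%: 81.6% (stated 82%)
- 154 per arm, 9% v 36.2%: 99.98% (stated 100%)

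These reproduce; the sample-size figures are not in question.

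**3. Sensitivity to false verification in one arm.** Suppose both incentive arms truly have p = 22.6%, and a share f of relapsed women in the 12-month arm only is falsely verified. The observed rate is p + (1 − p)f, so the false difference is 0.774f. The protocol gives no value for f, so a range is shown.

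| f (assumed) | False difference | Chance of p < 0.017, 154 per arm | 300 per arm |
|---|---|---|---|
| 2% | 1.5 points | 2.3% | 2.9% |
| 5% | 3.9 points | 5.6% | 9.9% |
| 10% | 7.7 points | 20% | 41% |
| 15% | 11.6 points | 45% | 78% |

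With f = 0 the chance is 1.7%. The whole planned 13.6 points would need f = 0.136/0.774 = 17.6%.

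**4. The same point in counts, also assumed.** At 154 per arm take 35 abstinent (22.7%) in the 3-month arm and a true 46 (29.9%) in the 12-month arm. Pearson chi-squared without correction:

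- 35 v 46: 308 × (35×108 − 46×119)² / (154 × 154 × 81 × 227) = 2.03, p = 0.1545.
- Add eight false verifications, 35 v 54 (35.1%): 308 × (35×100 − 54×119)² / (154 × 154 × 89 × 219) = 5.70, p = 0.0169.

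For 35 v 54 the unadjusted likelihood-ratio test gives 0.0166 and Fisher's exact test 0.023. The count 54 is the smallest that crosses 0.017; 53 gives 0.023 by Pearson. Eight women are 8/154 = 5.2% of the arm, but 8/108 = 7.4% of its assumed non-abstainers.

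**5. Do the stated analyses isolate this?**

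- The further secondary outcomes relax validation to self-report.
- The missing-data analyses ({20c}) concern unobserved outcomes, whereas a CO-only woman has an observed one.
- The sensitivity analysis of remote versus face-to-face consultations ({20b}) covers the setting, but separates neither CO-only verification nor the iCO cut-off.

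**The case against.** The case against is substantial.

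- **Some measures work against the route.** The retention section offers every arm £20 for an assessment that includes biochemical testing, and plans a reminder when posted saliva has not arrived. A reader might infer that a woman in the 12-month arm can withhold the kit unopposed; the document does not support that. It also does not say whether the £20 requires saliva, so the safeguard is partial.
- **A planned analysis is adjacent.** It would be wrong to say that nothing planned touches the issue, given the remote versus face-to-face analysis. It does not answer this question, however.
- **The fallback is narrow.** It applies where both tests cannot be collected, and a returned positive saliva test overrides a passing CO, subject to the anabasine step for nicotine users.
- **The iCO cut-off does not favour an arm.** One might infer that keeping < 8 ppm tilts the comparison. It applies equally to all arms and is openly disclosed, and < 8 ppm is described as more standard outside pregnancy. What stands is that the reasoning does not follow: a source recommending a lower cut-off is given as the reason for keeping a higher one.
- **The design is deliberate.** Incentives are meant to run up to the primary endpoint, and a fuller analysis plan is promised. Detail left to that plan is no fault. What is raised here is an outcome rule that the article fixes, two paragraphs that disagree, and a bias claim that the article asserts.

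**Conclusion.** The concern holds in limited form. The reward asymmetry at 12 months and the CO-only fallback are both in the text, the two paragraphs defining verification do not agree, and the low-bias statement is too strong for unblinded ascertainment with that fallback.

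The protocol does not show that bias will occur. Its size depends on the unknown number of CO-only verifications, and its direction is an inference from who is paid. The p-value example is not an estimate: both counts are assumed, it uses the smallest number that crosses 0.017, it puts no false verifications in the other arm, and Fisher's exact test stays above the threshold. It shows only that a handful of women could matter in the comparison with the least power. This calls for a worthwhile, inexpensive improvement and not a change of endpoint.

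**What to change.** Keep the primary definition. Then:

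1. Reconcile the two paragraphs under Primary outcome measure, so that it is clear whether CO alone verifies abstinence and whether a saliva sample that was requested but not returned counts as one that cannot be collected.
2. Before the treatment code is broken, pre-specify a sensitivity analysis of all three comparisons in which abstinence counts only with a confirming saliva result, and CO-only women count as not abstinent in every arm.
3. Tabulate verification route by arm: both tests, saliva only, CO only; and CO observed in person or taken on the home device.
4. Qualify the sentence under {17a}: verification route and the 12-month payment may differ by arm, and this will be examined as above.
5. As a secondary check, the same in all arms, repeat the analysis with iCO readings of 6 ppm or more counted as not validated, and repair the reasoning given for the cut-off.

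The cost is two extra analyses, one table and some rewording, using CO and saliva data already scheduled. The downside is that the saliva-confirmed analysis is conservative, because some truly abstinent women will not return a sample. It should be read as supportive only.

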### Secondary outcome measures

As a secondary outcome we will assess self-reported, lapse-free, smoking abstinence from the last quit attempt in pregnancy until 3 months postpartum, biochemically validated by an exhaled CO reading of < 8 ppm. Again, the proportion of abstinent women will be compared between the intervention and control groups. At both 3 and 12 months, for some women it may not be possible to conduct a test to biochemically validate self-reported abstinence (e.g. due to COVID restrictions). Therefore, as further secondary outcomes we will compare self-reported abstinence between the study groups at 3 and 12 months (including without biochemical validation as well as those with validation).

If a participant is recorded as having relapsed at 3 months postpartum, they will be automatically recorded as having relapsed for the primary outcome at 12 months postpartum, and will not be followed-up at 12 months.

In addition, in order to understand any differences between study groups, we will assess the following measures at three and 12 months postpartum (see Table 1):

**Table 1 Tab1:** Schedule of assessments

Assessment	Baseline	3 months postpartum	12 months postpartum
Demographics: age, education, occupation, ethnicity	X		
Smoking status: self-reported	X	X	X
Time since last smoking	X		
Expired CO level in ppm	X	X	X
Use of iCO single-person use CO monitor outside of assessments: self-reported		X	X
Cigarette consumption before pregnancy	X		
Self-efficacy for smoking cessation	X		
Use of nicotine products	X	X	X
Smoking in the home	X	X	X
Partner smoking status	X	X	X
Use of additional smoking cessation support	X	X	X
Whether they have a significant other supporter (SOS)	X		
Gestation	X		
Parity	X		
Breastfeeding intent	X		
Depression (Edinburgh Postnatal Depression Scale)	X		
Alcohol consumption: Alcohol Use Disorders Identification-Consumption (AUDIT-C) test	X		
Expired CO level in ppm	X	X	X
Saliva for cotinine/anabasine test			X

Use of nicotine products:
Have you used any nicotine replacement therapy (NRT) in the last week? Yes/noIf yes, which types of NRT have you mainly used? (Tick all that apply)Patch/lozenge/mouth spray/gum/microtabs/inhalator/nasal sprayHave you used an e-cigarette in the last week? Yes/noHave you used a heat-not-burn product in the last week (e.g. iQOS)? Yes/no

The assessment of use of nicotine products at 12 months postpartum also enabled us to consider the appropriateness of using a test of saliva cotinine vs anabasine, to determine smoking status, at this time.
Smoking in the home: Does anyone living in your home smoke tobacco? Yes/noPartner smoking status: If you have a partner, does your partner smoke tobacco? Yes/no/not applicableUse of additional smoking cessation support beyond that provided in the trial:

Are you currently receiving any professional help with stopping smoking other than the help you receive as part of this research study? Yes/no; if yes, which organisation is giving you this help?
Use of the iCO (single-person use) monitor beyond that required for the research assessments:

Have you used your iCO carbon monoxide monitor at times other than when asked to do so by your stop smoking advisor? Yes/no; if yes, on how many days have you used the iCO in this way since your baby was born? (Tick one box only) On 1 or 2 days/on 3 to 5 days/on 6 to 10 days/on 11 to 20 days/on more than 20 days

### Assessing smoking cessation outcomes during COVID-19 restrictions on face-to-face contact

During COVID-19, for the 3- and 12-month postpartum outcomes for smoking cessation, if it is not possible to take an expired CO reading during a face-to-face visit, participants will take a CO reading using a self-administered/single-person use device (iCO^TM^ Smokerlyzer, Bedfont Scientific Ltd.) [28] and send the CO reading to the stop smoking advisor via an app. There is recent evidence that the iCO can produce a slightly higher CO reading than more conventional CO monitors [20]. However, the authors of this study recommend an optimal cut-off for the iCO of < 6 ppm; therefore, we decided to retain our more liberal cut-off of < 8 ppm.

If a participant joined the trial before the COVID-19 restrictions and therefore was not sent a self-administered CO monitor when they were recruited and a face-to-face CO reading is not possible, then a CO reading will not be collected at 3 or 12 months follow-up; at 3 months, abstinence will be self-reported alone and at 12 months self-reported abstinence will be validated, where possible, by a saliva test. The participant will be sent a salivette and instructions to provide a saliva sample and will be advised how to take a saliva sample during the follow-up call with the stop smoking advisor. The participant will then be asked to post the saliva sample to a laboratory for analysis (ABS Laboratories, Hertfordshire, UK, https://www.acmgloballab.com/about-us/our-locations/europe-london-uk). The follow-up questionnaires will be administered by the participant’s stop smoking advisor over the phone. When the COVID-19 restrictions have been lifted, we will give participants the option of continuing with the above approach or they can choose to have face-to-face appointments.

### Economic measures

We will examine the incremental cost per quitter for the financial incentive interventions versus the no incentives group. We will collect resource and cost data (i.e. financial incentives, stop smoking service delivery) as well as considering rates of smoking cessation.

